#### Patient-Reported Outcomes Measurement Information System-Preference

The PROMIS (Patient-Reported Outcomes Measurement Information System)-Preference (PROPr) measures a participant’s health-related quality-of-life across the following PROMIS domains: cognitive function abilities, depression, anxiety, fatigue, pain interference, pain intensity, physical function, sleep disturbance, and ability to participate in social roles and activities [50-52]. The PROPr is also capable of generating a health utility index value, based on the participant’s scores for each domain, that represents the general US population’s preference for the respondent’s current health state. PROPr has 5 levels for each domain, ranging from “no problems” to “extreme problems.” The health-utility value produced by PROPr can range from –0.022 to 1, where 0 represents death, 1 represents perfect health, and values below 0 represent states perceived to be worse than death. The health-utility value is used to calculate quality-adjusted life-years (QALYs) [50,53].

### Statistical Analyses

#### Aim 1

The primary outcome of HIV care will be viral suppression (defined as less than 200 copies/mL). Secondary outcomes include the HIV-ASES, the HIV Treatment Optimism Scale, the ISSB, and urine drug screen results (test results for each of the 5 substances identified in the urine drug screen will be treated as different indicators). These outcome variables will be assessed at baseline and 3, 6, 12, and 18 months post enrollment. The resulting dependent variables will fall into one of two categories: (1) dichotomous variables (primary outcome: virologic suppression, and secondary outcome: urine drug screen results), assumed to follow a binomial distribution; or (2) continuous random variables (secondary outcomes: HIV-ASES, HIV Treatment Optimism Scale, ISSB scores), assumed to follow a normal distribution. All distributional assumptions will be evaluated prior to the conduct of analyses, and statistical methods chosen accordingly. Each of these dependent variables will be separately regressed on treatment condition (PHN alone vs SMS text messaging alone vs PHN+SMS text messaging), a set of baseline covariates (individual-level demographic characteristics), and time-varying covariates (social and structural determinants of health), using hierarchical linear regression where responses at each time point are nested within individuals. All analyses will be conducted on available study-related data from all participants, regardless of whether or when they drop out of treatment. The effect of interest will be a time × treatment condition interaction effect which will estimate the differential course and impact of the three intervention modalities over the follow-up period.

A generalized linear mixed model (GLMM) [54-56] will be used to conduct analyses of all outcomes following an intent-to-treat approach. The GLMM is an ideal statistical procedure for analyzing a broad class of longitudinal outcomes, including costs. As described above, key indicators of HIV care will be regressed on treatment conditions and a series of baseline and time-varying covariates. Treatment condition will be used to predict the slope of time, creating a time × treatment interaction term that is the effect of interest in the proposed study. We will also report on the relationships between time-varying covariates and the outcome measures, including time-shifted analyses where the value of the covariate at a previous timepoint is used to predict the outcome measure at a subsequent timepoint. Hypothesis testing for any given outcome will involve fitting the statistical model of interest and testing the effect of interest, as well as all other estimable effects in the model. We will use an iterative model-building approach where the simplest model is fit to the data first, and additional explanatory factors are added iteratively, in order of theoretical importance. Likelihood ratio tests are used to determine if the more complicated of the 2 models is a significant improvement over the simpler model. Variables of interest such as those specified in Aim 1 will always be included in the final model as the statistical tests of those parameter estimates (be they significant or nonsignificant) are of primary interest to this study.

#### Aims 2 and 3

The economic analyses will follow well-established guidelines [57-59]. The study will incorporate all resources or costs associated with the PHN, SMS text messaging, and PHN+SMS text messaging interventions from the health care sector, state policy maker, and societal perspectives [58-60]. The health care sector perspective includes all formal medical costs incurred by the system on behalf of participants, including the cost of the intervention, and participant out-of-pocket costs. The state policy maker perspective is crucial to informing resource allocation decisions on behalf of the public, who is primarily responsible for funding health care among this underserved population, given data indicating that most transgender women are either public health care insurance beneficiaries or uninsured [11,19]; moreover, the direct costs associated with criminal-legal resources, social safety-net programs, etc are paid for using public funds. In addition to the resources or costs included in the state policy maker perspective, the societal perspective accounts for those associated with untreated or undertreated HIV and comorbid conditions, such as premature mortality, reduced labor productivity, and those incurred by victims of crime [61,62].

The resources required to implement and sustain each intervention in a “real-world” setting (Aim 2) will be estimated using a detailed microcosting analysis, guided by a tailored version of the Drug Abuse Treatment Cost Analysis Program. The microcosting analysis will consist of gathering relevant administrative data and conducting semistructured interviews with site personnel in order to capture quantitative data regarding the resources (time and materials) used to deliver the interventions. The intervention implementation phase is considered to be the time period from conception (including planning activities) until the “steady state.” Resources will be categorized as “fixed start-up” (incurred once), “time-dependent” (recurring, but does not vary with the number of participants), and “variable” (used every time a participant is served). The site visits and initial interviews will be conducted early in the study (~6 months following the first randomization). Follow-up interviews will be conducted virtually upon the study reaching a “steady state” (~12 months following the initial interview), to identify the time-dependent and variable resources required to sustain the intervention. “Steady state” will be determined with the assistance of site personnel. Implementation and sustainment costs will be estimated by assigning nationally representative price weights to the identified resources [58]. Research-specific costs will be excluded.

After estimating the implementation and sustainment costs associated with each intervention (PHN, SMS text messaging, and PHN+SMS text messaging), the relative value of each will be estimated according to the stakeholder perspective. This process entails capturing all relevant resources used by participants in each arm, assigning nationally representative price weights to them, estimating the predicted mean costs, and testing for differences between resource categories. Estimating the incremental costs between arms according to resource category allows for a careful evaluation of the downstream savings resulting from improvements in HIV care and reductions in related risk behaviors. These include savings resulting from reduced usage of high-cost health care (eg, emergency department visits and inpatient stays) and criminal-legal resources, as well as increased labor and other forms of productivity. Price weights will be derived from sources reflecting national “real-world” costs faced by state policy makers and society.

The primary outcome of the cost-effectiveness analysis (Aim 3) will be the incremental cost-effectiveness ratio (ICER), which will be calculated as the incremental, predicted-mean cost of a given intervention relative to an alternative, divided by the incremental predicted-mean effectiveness of the 2 interventions. The primary measure of effectiveness for the economic evaluation will be QALYs. The secondary measure of effectiveness will be advancement along the HIV Care Continuum. The QALY is a measure that combines the health-related quality-of-life associated with an individual’s health state and the time spent in that state and is recommended as the primary effectiveness measure in economic evaluation studies due to its ability to be compared across interventions and disorders [58,63]. In addition, generally accepted thresholds for defining value have been established for QALYs, unlike clinical measures [64,65]. The HIV Care Continuum is an important and widely accepted model or tool for assessing HIV care outcomes at both an individual and a public health level; thus, the additional cost required to achieve a one-step increase along the HIV Care Continuum for the average transgender woman with HIV will be a critically important clinical and policy-relevant measure. Two ICERs (one for each effectiveness measure) will be calculated for each stakeholder perspective at both 3 months (intervention completion; immediate effects) and 18 months (distal effects).

To help address censored data, we will model the person period and estimate all regressions using a multivariable GLMM. Separate regressions will be estimated to predict the mean value for each resource category, at each time period, by study arm. The statistical method of recycled predictions will be used to obtain the final predicted mean values [58]. Similarly, individual regressions will be used to predict the health utility index value and HIV Care Continuum steps gained for each participant, at each time point. QALYs gained will be estimated using the predicted health utility values and the area under the curve methodology [58]. The most appropriate distributional and link functions for each GLMM regression will be chosen according to the fit of the observed data [58].

To account for sampling uncertainty in point estimates, the *P* values and SEs will be estimated using nonparametric bootstrapping techniques within the multivariable framework combined with methods to address missing data based on recommended approaches [66]. All monetary values will be adjusted for inflation, and all measurements obtained beyond 12 months of baseline will be discounted for time preference using the recommended rate of 3% [58,65].

The most cost-effective strategy for each outcome measure (QALYs; HIV Care Continuum placement) will be determined using the rules of strong and extended dominance. Parametric methods based on parameters obtained from bootstrapping will be used to estimate cost-effectiveness acceptability curves for each ICER, which illustrate the probability that an intervention is cost-effective for different value thresholds [57].

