The promising findings gleaned from our team’s two Health Resources and Services Administration-funded Special Projects of National Significance demonstration projects guided the Text Me, Alexis! randomized controlled trial design. Reback et al [33] demonstrated that increased attendance to PHN sessions was associated with significant and sustained (ie, through 18 months) achievement of both behavioral (coefficient range 0.12-0.38) and biomedical (coefficient=0.10) HIV milestones (all *P*≤.01); 85% were linked to HIV care, and 83% of the participants that enrolled detectable and achieved a 1 log viral load reduction went on to achieve viral suppression [28]. Additionally, Reback et al [24] produced significant and sustained (ie, through 18 months) overall increases in ART uptake, self-reported ART adherence as “excellent,” and achievement of an undetectable viral load defined as ˂200 copies/mL (49% vs 77%, 5% vs 38%, 35% vs 52%, all *P*≤.001) [25]. The Alexis Project has been included in the Substance Abuse and Mental Health Services Administration’s intervention guide for persons with substance use and mental health disorders, and Text Me, Girl! has been included in the Ryan White HIV/AIDS Best Practices Compilation. Thus, the appropriate next step was Text Me, Alexis!, the randomized controlled trial to simultaneously assess the relative efficacy of these interventions, and their respective costs and benefits to determine their efficiency and inform widescale implementation.

An economic evaluation was included to inform “real-world” resource allocation decisions faced by relevant stakeholders. Economic value (ie, the extent to which a stakeholder’s resources are efficiently allocated) is a fundamental concern for any intervention targeting transgender women with HIV, given the number of persons in need and the fact that services for transgender women are frequently delivered in resource-limited, community-based settings [3,19,20].

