### Participants

Inclusion criteria are (1) identifying as a transgender woman; (2) being 18 years or older; (3) having a verified HIV-positive serostatus; (3) not currently in HIV care, or had not had an HIV care visit in the previous 6 months, or had a viral load of ≥200 copies/mL on her last laboratory test result, or not currently prescribed ART, or prescribed ART but does not rate her ability to take all her medications as “excellent”; and (4) ability to receive daily SMS text messages on either a personal cell phone or via an email account. Potential participants must be able and willing to provide informed consent and comply with study requirements. Individuals are excluded if they do not meet all eligibility criteria.

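### As most naturally read, the Aim 1 model lets the arms differ in baseline viral suppression, which costs the primary test precision but not validity

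*Protocol article*

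**What the plan says.** The Statistical Analyses section of the protocol article (Aim 1) sets a binary primary outcome: "The primary outcome of HIV care will be viral suppression (defined as less than 200 copies/mL". On timing it states "These outcome variables will be assessed at baseline and 3, 6, 12, and 18 months post enrollment". The model is fitted "using hierarchical linear regression where responses at each time point are nested within individuals".

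On predictors it says "Each of these dependent variables will be separately regressed on treatment condition", together with "a set of baseline covariates (individual-level demographic characteristics") and time-varying social and structural covariates. The target is fixed as well: "The effect of interest will be a time × treatment condition interaction effect". The next paragraph adds that treatment predicts the slope of time and that the Aim 1 variables always stay in the final model. Baseline suppression or viral load is not named as a covariate, and no common baseline mean is imposed.

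Three other places bear on this:
- **Participants.** Several care-related alternatives are joined by *or*. One is that a woman is "prescribed ART but does not rate her ability to take all her medications" as excellent. A detectable viral load is a separate alternative, not a requirement.
- **Randomization.** The strata are age, race or ethnicity, and linkage to HIV care. Suppression is not one of them.
- **Background.** The earlier text-messaging project reports three pairs of percentages, "49% vs 77%, 5% vs 38%, 35% vs 52". The third pair is the share below 200 copies/mL.

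**The concern.** If every participant were unsuppressed at entry, the baseline response would be constant and its handling would not matter. Here it varies: suppressed women on ART can enroll, and about 35% were below 200 copies/mL at entry in the earlier text-messaging project, if its third pair is read as before and after.

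With a treatment main effect and baseline among the responses, each arm has its own estimated starting level. The interaction is then a within-person change contrast, exactly so in a balanced linear random-intercept model and approximately so in the logistic one. Randomization guarantees that the arms start equal in expectation, so the model spends information on a difference known to be zero. Three active arms with 65 women each leave little precision to spare.

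**Working it through.** **Inputs.** From the article: 65 per arm; visits at 0, 3, 6, 12 and 18 months; 35% and 52% from the Background. Assumed, because the article gives none: two-sided alpha 0.05, two arms compared, no dropout, compound symmetry with within-person correlation ρ from 0.2 to 0.8.

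**The plan's own figure.** N=195 comes from a simulation whose power, alpha, effect size and correlation are not in the article, so it cannot be reproduced. For orientation only, a two-proportion comparison at 65 per arm has 56% power for 52% vs 70% and 78% for 52% vs 75%.

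**Slope test (the stated effect).** For the five visits Σt = 39, Σt² = 513, mean 7.8, and Σ(t − 7.8)² = 513 − 39²/5 = 208.8. The variance of the between-arm slope difference is
- arms free at baseline: 2σ²(1−ρ) / (65 × 208.8)
- common baseline: 2σ²(1−ρ) / (65 × [513 − 1521ρ/(1+4ρ)])

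The ratio is R = [513 − 1521ρ/(1+4ρ)] / 208.8. At ρ = 0.5: (513 − 253.5)/208.8 = 1.24. If the common-baseline test has 80% power, the free test has Φ(2.802/√R − 1.960), and 65 × R per arm would restore 80%.

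**Average of the four follow-ups.** The corresponding ratio is 1.25(1−ρ) / [ρ + (1−ρ)/4 − ρ²]. At ρ = 0.5: 0.625/0.375 = 1.67.

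| ρ | Slope: R | Power | n per arm for 80% | Average: ratio | Power | n per arm for 80% |
|---|---|---|---|---|---|---|
| 0.2 | 1.65 | 59% | 107 | 2.78 | 39% | 181 |
| 0.3 | 1.46 | 64% | 95 | 2.27 | 46% | 148 |
| 0.5 | 1.24 | 71% | 81 | 1.67 | 58% | 108 |
| 0.7 | 1.12 | 76% | 72 | 1.32 | 69% | 86 |
| 0.8 | 1.07 | 77% | 70 | 1.19 | 73% | 77 |

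**If baseline is left out of the responses.** Consider the arm contrast at one follow-up. Without baseline its variance is proportional to 1; with baseline as a covariate, to 1−ρ². A test with 80% power after adjustment has Φ(2.802√(1−ρ²) − 1.960) without it: 78%, 76%, 68%, 52% and 39% at the same five correlations. Omission does not rescue the plan, and here the loss grows with the correlation.

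**Binary outcome.** A logistic random-intercept model was simulated with 400 trials per cell, a likelihood ratio test of the slope difference, and 35% baseline suppression in both arms. For a gradual effect reaching 52% vs 72% at 18 months, power with free vs common baseline was
- 47% vs 74% at random-intercept SD 1
- 59% vs 76% at SD 2
- 73% vs 82% at SD 3

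With no effect, the slope test rejected in 2.8–4.0% of trials (free) and 2.8–3.5% (common).

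**The case against.** The strongest reply has four parts.

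1. *The model is partly inferred.* The article does not say outright that baseline is a response row, and it describes the effect as running over follow-up. Visit coding and the full covariate list may be settled in an analysis plan not shown, and iterative model building could add baseline viral load. This stands as a limit on certainty. But the article does fix a treatment term, demographic baseline covariates and the interaction, and neither reading makes prespecified use of baseline suppression.
2. *The analysis is standard and valid.* This stands. The simulated type I error was not inflated, so the point is efficiency only.
3. *The penalty shrinks as suppression becomes more stable.* This stands. If baseline strongly predicts later suppression, the change-type analysis loses less: about 3 points of power for the slope at ρ = 0.8.
4. *Stratifying on linkage to care already helps.* Only in part, because women linked to care may or may not be suppressed.

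Two stronger readings are tempting. A reader might infer that the plan always discards much of its power. The slope results do not support that at high correlation, and the larger losses belong to an average post-baseline contrast, which is not the stated test. A reader might also infer that a chance baseline imbalance is subtracted in full. For a slope it is not: in the linear model a deviation at baseline alone shifts the fitted 18-month change by 18 × 7.8/208.8 = 0.67 of its size, and an imbalance that persists through follow-up cancels.

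**Conclusion.** The concern holds as a loss of precision. For the stated slope test the loss is 3 to 9 points of power at correlation 0.5 to 0.8 and 16 to 21 points at 0.3 to 0.2, from an 80% reference. It exists at every correlation examined and is small if suppression is very stable. It would be larger for an average post-baseline contrast (power 39% to 73%).

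These sizes rest on compound symmetry, complete data, a linear approximation for the main table, and assumed effect sizes and correlations. They do not show that the trial is underpowered, since the article does not state the design power. That baseline is a response row is the natural reading, not an explicit statement.

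**What to change.** Prespecify one of two forms before the primary analysis:
- **Common baseline.** Keep baseline as a response, give all arms one baseline mean, and let them differ only after baseline.
- **Baseline as covariate.** Use the 3- to 18-month visits as responses, with baseline suppression or log viral load as a covariate. The treatment effect must then be read from the arm differences at those visits, because a slope from month 3 onward would miss an effect already present at month 3.

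Do the same with the baseline values of HIV-ASES, the HIV Treatment Optimism Scale, ISSB and the urine drug screens for the secondary outcomes. Reporting results by baseline suppression is an optional extra.

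The cost is analysis wording only. Biospecimens and the baseline assessment come before randomization, and viral load is tested at every time point, so no new data or participants are needed.

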### Primary and Secondary Aims

The primary aim of the Text Me, Alexis! study is to determine the comparative effectiveness of PHN alone, SMS text messages alone, and PHN+SMS text messaging combined with the goal of viral suppression and cost-effectiveness, and to identify the resources (eg, time and materials) required to prepare for, implement, and sustain each intervention, and estimate the associated costs. Further, the study will conduct a comprehensive cost-effectiveness analysis to determine the relative value of each intervention from the health care–sector, state policy makers, and societal perspectives. The secondary aim of the study is to determine heterogeneous intervention effects of PHN alone, SMS text messaging alone, and PHN+SMS text messaging due to social and structural determinants of health (eg, poverty, housing insecurity, food scarcity, educational attainment, and lack of insurance) and differing individual-level characteristics (eg, racial or ethnic identity, age, SUD—by type, and time since HIV diagnosis) among transgender women with HIV.

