### Study Arms

#### PHN

PHN is based on the theoretical foundation of social cognitive theory (SCT). Participant-centered PHN helps to (1) identify barriers to HIV care, (2) identify and link participants to needed auxiliary services, and (3) increase participants’ self-efficacy in working with HIV care providers and other social service and treatment facilities. PHNs do not provide counseling or psychotherapy; they work with each participant to successfully navigate complicated health care and social service systems. The PHN intervention uses an individualized, participant-centered treatment plan with the goals of removing multiple and complex barriers that can impede linkage to and retention in HIV care and medication adherence to achieve virological suppression. Each participant works with a PHN to develop a participant-centered treatment plan and get linked to HIV care or other needed auxiliary physical, mental health, and psychosocial services (eg, hormone therapy, dental care, hepatitis testing or care, SUD treatment, mental health treatment, legal services, and job training or development; Figure 2). A priority of the first session is to schedule an HIV care appointment for the participant if needed. The PHN also works with each participant to establish HIV self-efficacy regarding her treatment plan. To establish an immediate connection, participants are introduced to a PHN immediately following randomization. PHN sessions are unlimited for 90 days.

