### Challenges

There are several challenges to the Text Me, Alexis! study. First, housing instability, substance use, engagement in sex work, and other individual-level, social, and structural disparities may interfere with study participation. The PHN alone and PHN+SMS text messaging arms were designed to address these issues and work with each participant to assess and minimize or remove barriers and link participants to an array of ancillary social services. Additionally, in the demonstration project, despite experiencing several health disparities including low educational attainment, low income, and housing instability, SMS text messaging alone demonstrated significant improvements in ART uptake, ART adherence, and achievement of an undetectable viral load, which were durable through 18-month follow-up. Second, episodes of short-term incarceration may interrupt study progress and follow-up assessment rates, due to factors such as actual or perceived participation in the street economy, or minor homeless infractions. Study staff monitor the public records database for participants who miss appointments. When an incarcerated participant is found, we begin a correspondence with the participant immediately upon release. Third, loss of ART or selling ART due to lifestyle needs (“diversion”)—ART adherence will be stressed through the participant-centered treatment plan and via adherence-specific SMS text messages, including strategies for keeping medication safe, and a discussion on how ART adherence outweighs selling the drug. Finally, fear of drug-drug interaction—some participants may be concerned about ART and gender-affirming hormone therapy interactions and prioritize gender-affirming hormone therapy over ART uptake or adherence. These concerns will be acknowledged and corrected in PHN sessions and SMS text messages.

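### The primary model for viral suppression adjusts for post-randomisation social and structural determinants that navigation is designed to change, so it does not estimate the total effect of PHN against SMS

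*Protocol article*

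**What the plan says.** The outcome is fixed under Statistical Analyses, Aim 1: "The primary outcome of HIV care will be viral suppression (defined as less than 200 copies/mL"). Each outcome is regressed on arm, on baseline covariates described as individual-level demographics, and on "time-varying covariates (social and structural determinants of health), using hierarchical linear regression where responses at each time point are nested within individuals". The text itself separates the two kinds of covariate: demographics are baseline, determinants are time-varying. The effect of interest is the time by treatment interaction from this regression. The paragraph on the generalized linear mixed model repeats the structure under an intent-to-treat label: "key indicators of HIV care will be regressed on treatment conditions and a series of baseline and time-varying covariates".

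On model building, "the simplest model is fit to the data first, and additional explanatory factors are added iteratively, in order of theoretical importance", with likelihood ratio tests between successive models. The article adds: "Variables of interest such as those specified in Aim 1 will always be included in the final model".

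The Primary and Secondary Aims section shows what the determinants are, where it plans to study effects that differ "due to social and structural determinants of health (eg, poverty, housing insecurity, food scarcity, educational attainment, and lack of insurance").

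On how navigation works, the PHN section gives the goal of "removing multiple and complex barriers that can impede linkage to and retention in HIV care". The Challenges section names housing instability and other social and structural disparities, then says the PHN and PHN+SMS arms were "designed to address these issues and work with each participant to assess and minimize or remove barriers".

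**The concern.** The primary aim is the comparative effectiveness of three randomised strategies. That is a total effect: everything that follows from assignment, by whatever route. A determinant measured at 3, 6, 12 or 18 months can itself be a result of assignment. On the article's own account of navigation, housing and similar barriers lie on the path from PHN to suppression, in two arms and not in the third.

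Holding such a variable fixed has two consequences. It takes out the part of the effect that runs through the variable. And if something unmeasured drives both the determinant and suppression, conditioning on the determinant links that cause to arm, so randomisation no longer protects the comparison.

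At stake are the two contrasts with SMS alone, where resource decisions depend on whether the more intensive intervention does better. PHN vs PHN+SMS should be less affected, because both arms contain navigation.

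**Working it through.** **Plan's own figure.** None bears on this point. The sample size adds up (3 × 65 = 195), but the power section states no alpha, power, effect size or dropout, so nothing further can be reproduced. What follows is an illustration, and every input is an assumption.

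**Set-up.** PHN vs SMS at one follow-up visit, with a binary barrier M.
- Prevalence of M: 50% under SMS; 50% minus d under PHN, with d = 0, 10, 20 or 30 points.
- Log-odds of suppression = 0.3 + 0.4 × PHN − b × M, with b = 0.7, 1.1 or 1.6.
- Optional unmeasured common cause: a standard normal variable that lowers the barrier (coefficient 1.0 on its latent scale) and raises suppression (0.7 on the log-odds).

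**One case by hand (d = 20 points, b = 1.1, no common cause).** With expit(x) = 1/(1 + e^−x): expit(0.3) = 0.574, expit(−0.8) = 0.310, expit(0.7) = 0.668, expit(−0.4) = 0.401.
- SMS: 0.5 × 0.574 + 0.5 × 0.310 = 0.442.
- PHN: 0.7 × 0.668 + 0.3 × 0.401 = 0.588.
- Total risk difference: 0.588 − 0.442 = 0.146.
- Adjusted for M, standardised to its pooled prevalence of 40%: 0.6 × (0.668 − 0.574) + 0.4 × (0.401 − 0.310) = 0.056 + 0.036 ≈ 0.093.
- Share removed: 1 − 0.093/0.146 ≈ 36%.

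A simulation of 400,000 participants gives 0.147 and 0.094, also 36%. The log odds ratio falls from 0.592 to 0.404.

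**Share of the risk difference removed by adjustment (simulation; b = 0.7 / 1.1 / 1.6)**

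| Barrier lowered by | No common cause | Same-direction common cause |
|---|---|---|
| 0 points | about 0% throughout | about 0% throughout |
| 10 points | 15 / 23 / 30% | 33 / 41 / 46% |
| 20 points | 26 / 36 / 46% | 59 / 65 / 70% |
| 30 points | 35 / 46 / 56% | 77 / 81 / 85% |

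**Link to the stated effect of interest.** Randomisation makes the expected arm difference zero at baseline. In a two-visit logistic model with fixed effects only and a constant effect of M, the time by arm coefficient is therefore the follow-up log odds ratio minus zero. In the example it moves from about 0.59 to about 0.40. The interaction does not escape the problem.

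**Can the sign reverse?** If the whole effect runs through M (direct coefficient 0) and there is no common cause, the adjusted difference is exactly 0, because PHN and SMS then have the same risk within each level of M. A negative value needs an unmeasured common cause as well.

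**Power, for context.** At 65 per arm, an assumed two-sided alpha of 0.05 and an SMS rate of 0.44, a simple two-proportion comparison has about 39% power for a difference of 0.147 and about 19% for 0.094. This is not the power of the planned repeated-measures model.

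**The case against.** **Navigation may not move these determinants.** It lasts 90 days. The service examples in the PHN section include legal help, job training and substance use treatment, but not housing, food or insurance, and educational attainment is unlikely to change. This stands as a limit on size: with no change in the determinant, nothing is lost. It does not rescue the model. The Challenges section gives housing instability among the issues the navigation arms were designed to address, outcomes run to 18 months, and a primary analysis should not be sound only if the intervention's mechanism fails.

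**A simpler model is fitted first.** A less adjusted estimate will probably exist, but the article does not make it the basis of inference. Whether the determinants must stay in the final model is ambiguous: the retention sentence refers to Aim 1 variables, and the determinants are listed under Aim 1 in Statistical Analyses, yet the aims section names them only in the secondary aim. On either reading, no baseline-only model is designated as primary.

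**The illustration is simpler than the planned model.** True: it has one follow-up visit, no participant random effect and no baseline outcome. It shows the mechanism and a plausible range, not a forecast.

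**Stronger readings that a reader might infer, but that the text does not support:**
- That the likelihood ratio step picks out the strongest mediators. Terms enter by theoretical importance, and if the determinants are always retained the test does not select them.
- That visits with a health-record viral load but no interview would be dropped. The Viral Load Test section lets a record result replace the study's assay within 14 days of an assessment; it does not describe an outcome without an assessment.
- That the heterogeneity aim uses post-randomisation determinants as modifiers. The article does not say which values it will use.

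**Conclusion.** The point holds as a fault in the stated analysis, not as a detail left to a later plan. The article puts post-randomisation determinants into the model that yields its primary effect, and its own account of navigation places at least some of them on the causal path. Followed as written, the model does not estimate the total comparative effect that the primary aim asks for. The determinants of concern are housing, food, income and insurance.

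The size is not derivable from the article. The range of about 15% to 56% without a common cause, and about 33% to 85% with a same-direction one, rests on the assumed inputs above, including that navigation lowers a barrier by 10 to 30 points. If it does not, the loss is about nil.

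A reader might go further and infer that the analysis is certain to favour SMS, or that it would reverse the sign. The documents support neither. Attenuation of the navigation effect is the expected direction, but confounding between determinant and outcome could shift the bias either way, and the article gives no information on such confounding.

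**What to change.** State one primary model and name it as the basis for inference: arm, visit, arm by visit, the three stratification factors from the Randomization section (age group, race or ethnicity group, HIV Care Continuum placement), and baseline covariates only. Baseline values of the determinants may be included, which keeps whatever precision they offer without conditioning on anything affected by assignment.

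Move the post-baseline determinants, including the time-shifted analyses, to a separate secondary analysis, labelled either as descriptive and non-causal or as a mediation analysis with its assumptions stated. Reword the sentence on retained variables so that it cannot be read as forcing post-baseline determinants into the primary model.

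The cost is analysis wording. The outcomes are already assessed at baseline, no procedure or sample size changes, and the planned time-varying analyses are kept as secondary. The article expects data collection to end in July 2027, with primary analyses after that, so the change can be documented before they begin.
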